## Abstract

**Background:**

Healthy Together Victoria (HTV) - a complex ‘whole of system’ intervention, including an embedded cluster randomized control trial, to reduce chronic disease by addressing risk factors (physical inactivity, poor diet quality, smoking and harmful alcohol use) among children and adults in selected communities in Victoria, Australia (Healthy Together Communities).

**Objectives:**

To describe the methodology for: 1) assessing changes in the prevalence of measured childhood obesity and associated risks between primary and secondary school students in HTV communities, compared with comparison communities; and 2) assessing community-level system changes that influence childhood obesity in HTC and comparison communities.

**Methods:**

Twenty-four geographically bounded areas were randomized to either prevention or comparison (2012). A repeat cross-sectional study utilising opt-out consent will collect objectively measured height, weight, waist and self-reported behavioral data among primary [Grade 4 (aged 9-10y) and Grade 6 (aged 11-12y)] and secondary [Grade 8 (aged 13-14y) and Grade 10 (aged 15-16y)] school students (2014 to 2018). Relationships between measured childhood obesity and system causes, as defined in the Foresight obesity systems map, will be assessed using a range of routine and customised data.

**Conclusion:**

This research methodology describes the beginnings of a state-wide childhood obesity monitoring system that can evolve to regularly inform progress on reducing obesity, and situate these changes in the context of broader community-level system change.

## Background

Childhood obesity immediately and distally impacts physical and psychological health [1, 2]. The stubbornly high prevalence of obesity globally [3], and persistence of childhood obesity into adulthood [2, 4], with resultant increased morbidity and mortality [5], highlights the imperative to develop effective prevention and monitoring strategies for childhood obesity.

Evidence [6–8] of success in preventing childhood obesity [6, 7] in a variety of specific settings (e.g., school-based [8–10], community-based [11], home-based [12],) is tempered by challenges in sustaining the long-term impact of these interventions and applying the interventions at the population level [6]. The most recent Cochrane review of obesity prevention [6] has identified that multifaceted and multilevel strategies are required to prevent obesity. The Foresight Obesity Systems Map [13] provides corroboration for this assessment through the visualization of obesity as a complex systems problem [14]. Support is growing for population level efforts to prevent childhood obesity to apply systems thinking [15] in the expectation that systems thinking may improve intervention implementation, effectiveness and sustainability of changes. To date, no known initiative has applied a ‘whole of systems’ approach to prevent childhood obesity [16]. Healthy Together Victoria’s (HTV) large-scale complex whole of system approach to the primary prevention of chronic disease, in the state of Victoria, Australia is a world first. Taking a population-level approach to reducing chronic disease and specifically obesity through improving associated determinants (physical inactivity, poor diet quality, smoking and harmful alcohol use) among children and adults in the specific communities where they “live, learn, work and play” [17]. Due to the broad scope and the adaptive nature of HTV, detailed methods are beyond the remit of this article but can be found at http://www.healthytogether.vic.gov.au/resources/index.

Commencing in 2012, HTV’s multi-faceted intervention includes a boosted capacity at the local level of >170 staff in 12 communities [18]. These personnel were employed to support and deliver ‘system activation’ for healthy environments and healthy living in schools, early childhood settings, workplaces and communities through a variety of means. Systems activation refers to initiating actions on the systems that influence the health and well-being of individuals, families and communities. These actions include delivering multiple strategies, policies and initiatives at both the state and local levels to target all Victorians. Complementing the state-wide systems activation and programs, HTV also contributes resources and effort towards improving the health of children through a quality framework to support the creation of healthier school environments through a range of services such as the Healthy Together Victoria Achievement Program and Healthy Eating Advisory Service and is complemented by a range of community based healthy living programs and state-wide and local social marketing of health promotion messages.

HTV includes a cluster randomized trial of the ‘whole-of-system’ intervention. With increasing intervention complexity, evaluation approaches require a degree of flexibility in order to accordingly engage with complexity. In this paper, we outline the methodological approaches that will be taken to comprehensively measure the impacts of HTV on childhood obesity through two parallel research programs with the following aims:To measure the impacts of HTV on anthropometry and obesogenic behaviors among Victorian children and the environments in which they live, learn and playTo measure the effects of change to community-level system factors on rates of childhood obesity among Victorian children.

## Methods/design

### Setting

Healthy Together Victoria, an initiative of the State Government of Victoria, was initially funded in partnership with the Commonwealth Government of Australia [17]. Victoria is a state of approximately 5.8 million people in the South-Eastern region of Australia [19]. As described above, the centrepiece of HTV is a funded workforce of approximately 170 people across the state in local government, community health and non-government organisations whom take a range of actions at the community and state level [18]. These actions are varied but can include: policy and leadership for health promotion; providing quality improvement frameworks for early childhood services, schools and workplaces; supporting policy development/implementation and targeted strategies within settings; working with food growers, producers and sellers to increase access to healthy food, especially disadvantaged populations; working with urban planning to support active transport; working with sport and recreation centres to increase healthy food access; building leadership for prevention; and social marketing of health promotion messaging www.healthytogether.vic.gov.au [18]. The cluster randomized trial, embedded within the wider HTV initiative, includes 12 prevention areas spread across 14 local government authority (LGAs) (Healthy Together Communities) and 11-matched comparison areas spread across 12 LGA’s in Victoria, Australia (with one comparison community acting as a matched comparator for two prevention areas). Matched randomisation of clusters was based on socio-demographic indices [Socioeconomic Index for Areas (SEIFA)] [20] and chronic disease risk factor prevalence (i.e., unhealthy weight)] of adults within participating LGA’s and was conducted by the Department of Health and Human Services (Victoria). The wider HTV evaluation has a multitude of components, several of which are outlined in Table 2. The methodology described here captures (1) how the core primary and secondary outcomes will be measured and (2) how these relate to community-level system change.

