### Study design, sampling and sample size

Standard approaches for sample size calculations within cluster randomized trials were made (in GenStat V14.2) based on the comparison of Body Mass Index standardized for age and sex (BMI-z) [21] scores between intervention (12 clusters) and comparison (12 clusters) communities using power of 0.8 and 0.05 for significance test. The clustered trial involves intervention at the area level and thus an intra-class correlation of 0.1 for the BMI-z was used, based on previous school-based research [22–24]. Baseline BMI-z (0.65) and standard deviation (0.93) were taken from our previous studies of >1800 [22] school children and the expected change in BMI-z over the 4 years was set to 0.18. The justification for this estimated change over 4 years of 0.18 is based on the findings from our previous interventions within the same age groups (primary [22] and secondary students [24]) and was associated with a 3 percentage point reduction in overweight and obesity in these populations.

Using the parameters above, the sample size calculations indicated a need for ≥ 25 children in each of the 4 year levels (Grade 4, Grade 6, Grade 8 & Grade 10) to be assessed in each intervention/comparison area to determine significant differences in BMI-z score between intervention and comparison communities. A repeat cross-sectional design will assess all participating students in each grade level per intervention and comparison community and repeated samples of students on a biennial basis in 2014, 2016 and 2018 during Term 3 (Jul - Sept) of the Victorian School Term (giving a total of approximately >7,200 children assessed once).

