### Data analysis

Cross-sectional (within year) and longitudinal (across region/LGA) multilevel analyses will be conducted to consider different exposure variables (condition) and the effects of clustering (within school, between LGA) and other potential confounders (age, gender, socioeconomic position). A multilevel growth model [50] will be used to examine how BMI z-score, and other dependent variables (physical activity, sedentary behavior, diet quality, wellbeing), change over the three waves of data collection. A growth model will be used because it accommodates; 1) modelling of change over time; and, 2) simultaneous modelling of change occurring within an LGA over time, and between LGAs over time.

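### The article gives 24 areas (12 v 12) in the abstract and sample size but 23 (12 v 11, one shared comparator) in the Setting section, and the stated Aim 1 model could use the matching at little cost

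*Protocol article*

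**What the plan says.** Three places in the protocol article give the number of areas.

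- **Abstract, Methods:** "Twenty-four geographically bounded areas were randomized to either prevention or comparison (2012").
- **Study design, sampling and sample size:** the calculation compares "intervention (12 clusters) and comparison (12 clusters) communities". It asks for at least 25 children in each of four year levels per area. With waves in 2014, 2016 and 2018, it arrives at a total of more than 7,200 children, each measured once.
- **Setting:** the trial has 12 prevention areas in 14 LGAs and "11-matched comparison areas spread across 12" LGAs, "with one comparison community acting as a matched comparator for two prevention areas".

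On allocation, the Setting section says "Matched randomisation of clusters was based on socio-demographic indices" (SEIFA) and on chronic disease risk factor prevalence in adults, with unhealthy weight as the named example.

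On analysis, the Aim 1 Data analysis section describes multilevel models with clustering by school and LGA, adjustment for "other potential confounders (age, gender, socioeconomic position"), and a growth model for change in BMI-z over the three waves. It mentions neither the matched sets nor adult unhealthy weight.

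**The concern.** The number of randomised units is a basic fact of a cluster trial, and it drives power far more than the number of children does. Here the abstract and the sample size disagree with the description of the design. If the Setting section is right, the total counts the shared comparator twice, although each child is supposed to be counted once.

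The second issue is how the matching enters the analysis. The areas were matched on variables thought to predict the outcome. The Aim 2 section on study design and sampling itself expects adult and child BMI to be correlated at LGA level, to a medium or strong degree. A model with no term for the set or for adult unhealthy weight may leave usable information aside, and with 23 clusters precision is scarce.

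**Working it through.** **1. Number of areas.** Setting: 12 + 11 = 23. Its LGA counts, 14 + 12 = 26, agree with the 26 LGAs in School and participant recruitment, so the LGA count gives no support for a 24th area. If every other comparison area has one partner, the sets are ten pairs and one triplet: 10 + 2 = 12 prevention areas and 10 + 1 = 11 comparison areas, in 11 sets.

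**2. Total number of children.** Per area and wave: 25 × 4 = 100.

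- 24 areas: 100 × 24 × 3 = 7,200, which reproduces the stated figure exactly.
- 23 areas: 100 × 23 × 3 = 6,900, which is 300 fewer (300 / 7,200 = 4.2%).

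**3. Standard error.** With equal cluster sizes the SE is proportional to √(1/k₁ + 1/k₂). The ratio of 12 v 11 to 12 v 12 is √[(1/12 + 1/11) / (2/12)] = √(0.17424 / 0.16667) = 1.022, a rise of 2.2%.

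**4. Power.** Suppose the 12 v 12 design truly had 80% power, two-sided at 0.05 (the article does not state sidedness). The standardised effect is then 1.96 + 0.8416 = 2.8016. For 12 v 11 it is 2.8016 / 1.0225 = 2.740, and power is Φ(2.740 − 1.96) = Φ(0.780) = 78.2%. A t version (22 and 21 df) gives 78.1%.

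**5. Taking the stated inputs literally.** Use SD 0.93, ICC 0.1 at area level, 100 children per area and a difference of 0.18 in a single cross-sectional comparison. The design effect is 1 + 99 × 0.1 = 10.9.

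- 12 v 12: SE = 0.93 × √[(10.9/100) × (2/12)] = 0.1253, power 30.0%.
- 12 v 11: SE = 0.1282, power 28.9%.

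The miscount again costs about one point. On this reading the requirement of 25 per year level does not reproduce at all. That is a separate matter. It means I can give the relative effect of the miscount but not a corrected number per year level.

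**6. Matching factors against the stated Aim 1 model.**

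- SEIFA: covered in part, since socioeconomic position is a covariate.
- Adult unhealthy-weight prevalence: not named for Aim 1. Adult anthropometry is brought in only for the Aim 2 models.
- Matched set: not named.

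**7. Cost of a set term.** In an area-level analysis with sets fixed, the residual df would fall from 23 − 2 = 21 to 23 − 11 − 1 = 11. The critical t would rise from 2.080 to 2.201, or 5.8%. A random set effect should cost less.

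**The case against.** **The count has little consequence.** The total is a floor, and the plan is to measure all participating students in up to six schools per area, so recruitment may well exceed it. The loss of power is about two points at most in the comparisons above. This stands as to size. It does not remove the contradiction: a statistical analysis plan may explain the count, but it leaves the published abstract and sample-size paragraph as they are.

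**Twenty-four may count something else.** It could mean 12 matched slots per arm with one area used twice, or 24 areas of which one was later lost. Either is possible. The first conflicts with the abstract's statement that 24 areas were randomised, and the second is nowhere reported. The article does not show which count is right, so the fix must allow for an explanation.

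**The analysis paragraph is short, and no statistical analysis plan is shown.** A reader might infer that the analysis discards the matching. The text does not say so: it names no set term, which is not the same thing, and it adjusts for a proxy of one matching factor. A reader might also infer a large loss of precision from the usual formula for matched comparisons. That formula concerns area means under an assumed within-set correlation. Aim 1 tests relative change in a growth model, where stable differences in level between areas largely cancel. The relevant quantity is the within-set correlation of area trends, and the article gives no value for it.

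**Double use in the analysis.** A reader might infer that the shared comparator will be analysed twice. No pairwise analysis is planned for Aim 1. The area-by-area matched estimates in Table 2 belong to the Preventive Health Survey. The double count shown here is in the planned total only.

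**Conclusion.** The contradiction in the number of areas is certain and rests on the article alone: 23 in the Setting section, 24 in the abstract and sample size. The total of 7,200 holds only for 24 areas; 23 areas give a minimum of 6,900. The effect on precision is small: SE up 2.2%, and about 78% power if 12 v 12 truly gave 80%. This assumes equal cluster sizes and a two-sided test.

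The point about matching is a recommendation. The stated Aim 1 model leaves out the matched set and one of the two kinds of matching variable. Including them should help efficiency by an amount that the documents do not allow one to quantify for change in BMI-z. Leaving them out does not make the comparison invalid.

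**What to change.** 1. Reconcile the passages. State 12 v 11 (23 areas) and a minimum of 6,900 children in the abstract and the sample-size paragraph, or explain the 24th area and how the shared comparator arose.
2. Redo the sample size on the reconciled count.
3. In the Aim 1 model, include matched set as a random effect (ten pairs and one triplet, with the shared comparator entered once). Alternatively, adjust for both matching variables, SEIFA and adult unhealthy-weight prevalence, as measured before 2012.

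The first two changes cost a few words and one recalculation. The third costs one model term and some degrees of freedom, kept low by fitting the set as random. No new data collection is needed: the matching variables were already used to randomise.

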### Research plan aim 1: to measure the impacts of HTV on anthropometry and obesogenic behaviors among Victorian children and the environments in which they live, learn, and play

Under aim one it is hypothesized that:School children in intervention LGAs compared with those in comparison LGAs will record relative decreases in BMI z-scores of at least 0.18 over the measurement period,The prevalence of overweight/obesity among school children in intervention LGAs will decrease over the intervention period, compared to those in the comparison LGAs, andThe levels of physical activity will increase, sedentary behavior will decrease and diet quality will improve over the intervention period among school children in the intervention LGAs compared with those in the comparison LGAs.

### Study design, sampling and sample size

Standard approaches for sample size calculations within cluster randomized trials were made (in GenStat V14.2) based on the comparison of Body Mass Index standardized for age and sex (BMI-z) [21] scores between intervention (12 clusters) and comparison (12 clusters) communities using power of 0.8 and 0.05 for significance test. The clustered trial involves intervention at the area level and thus an intra-class correlation of 0.1 for the BMI-z was used, based on previous school-based research [22–24]. Baseline BMI-z (0.65) and standard deviation (0.93) were taken from our previous studies of >1800 [22] school children and the expected change in BMI-z over the 4 years was set to 0.18. The justification for this estimated change over 4 years of 0.18 is based on the findings from our previous interventions within the same age groups (primary [22] and secondary students [24]) and was associated with a 3 percentage point reduction in overweight and obesity in these populations.

Using the parameters above, the sample size calculations indicated a need for ≥ 25 children in each of the 4 year levels (Grade 4, Grade 6, Grade 8 & Grade 10) to be assessed in each intervention/comparison area to determine significant differences in BMI-z score between intervention and comparison communities. A repeat cross-sectional design will assess all participating students in each grade level per intervention and comparison community and repeated samples of students on a biennial basis in 2014, 2016 and 2018 during Term 3 (Jul - Sept) of the Victorian School Term (giving a total of approximately >7,200 children assessed once).

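### The printed sample-size inputs give about 28% power for the comparison described, not 80%, and the level at which the ICC of 0.1 applies is unclear

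*Protocol article*

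**What the plan says.** The section on study design, sampling and sample size in the protocol article describes a standard cluster-trial calculation comparing BMI-z between "intervention (12 clusters) and comparison (12 clusters) communities using power of 0.8 and 0.05 for significance test". The ICC is introduced as follows: "The clustered trial involves intervention at the area level and thus an intra-class correlation of 0.1 for the BMI-z was used". The same sentence takes the value from earlier school-based research. The spread comes from earlier work: "Baseline BMI-z (0.65) and standard deviation (0.93) were taken from our previous studies". The expected change over four years is 0.18. The result is a requirement of at least 25 "children in each of the 4 year levels (Grade 4, Grade 6, Grade 8 & Grade 10") in each area, which is 4 × 25 = 100 children per area per wave. The quoted total of more than 7,200 agrees with this: 24 areas × 100 × 3 waves = 7,200.

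Three other places bear on the point:

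- Setting describes 12 prevention areas but 11 comparison areas, "with one comparison community acting as a matched comparator for two prevention areas", and says that areas were matched before randomisation.
- The first hypothesis under Aim 1 is about "relative decreases in BMI z-scores of at least 0.18 over the measurement period".
- The Aim 1 data analysis section plans a multilevel growth model over three waves.

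**The concern.** When areas are randomised, variation between areas sets a floor on the standard error that sampling more children cannot lower. At an area-level ICC of 0.1 and 12 areas per arm, that floor is already 0.120, so a difference of 0.18 is only 1.5 standard errors. A requirement of 25 children per grade therefore cannot be the result of the inputs printed beside it.

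Two further features make the calculation hard to interpret. The ICC comes from school-based research but is attached to the area, and the two levels are not separated. The calculation is also described as a comparison of scores between arms, whereas the hypothesis and the growth model concern a difference in change, which has a different variance.

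This is the only quantitative justification given for the size of the study. If it stands, a null result on BMI-z would be read as coming from a trial with 80% power for 0.18, which the stated inputs do not support.

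**Working it through.** **Inputs.** From the sample-size section: difference 0.18; SD 0.93, so variance 0.8649; ICC 0.1; 12 areas per arm; 100 children per area; significance 0.05. Sidedness is not stated, so two-sided is assumed. From Setting: 12 v 11 areas. From the recruitment section: three primary and three secondary schools per area.

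**1. The plan's figure, as printed (12 v 12, ICC at area level).**
- Variance of an area mean = 0.8649 × (0.1 + 0.9/100) = 0.8649 × 0.109 = 0.0943.
- SE of the arm difference = √(2 × 0.0943/12) = 0.1253.
- 0.18/0.1253 = 1.44.
- Power = 27.9% (noncentral t, 22 df) or 30.0% (normal).

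The stated 80% is not reproduced. The design effect gives the same answer: 1 + 99 × 0.1 = 10.9, so 1,200 children per arm have an effective size of 1,200/10.9 = 110. About 420 per arm would be needed without clustering.

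**2. Ceiling for this comparison.** With unlimited children per area, SE = √(2 × 0.8649 × 0.1/12) = 0.120 and the ratio is 1.50. Power is 30.0% (t) or 32.2% (normal).

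**3. With 12 v 11 areas.** SE = √(0.0943 × (1/12 + 1/11)) = 0.128. Power is 26.8% (t). The difference detectable with 80% power is about 0.38 (t); for 12 v 12 it is 0.37.

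**4. Other readings of the same inputs.**

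| Reading (12 v 12, t) | Power |
|---|---|
| 25 children as the area total | 23% |
| Three waves pooled, 300 per area | 29% |
| One-sided test, 100 per area | 40% |
| 48 area-by-grade groups per arm treated as independent, two-sided | 72% |
| The same, one-sided | 82% |

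The last two rows ignore the correlation between grades in the same area.

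**5. If 0.1 is a school-level ICC.** With six schools per area and area ICC a, the variance of an area mean = 0.8649 × [a + 0.1/6 + (0.9 − a)/100]. At a = 0 this is 0.0222.

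| Area ICC (assumed) | 12 v 12 (t) | 12 v 11 (t) |
|---|---|---|
| 0 | 81% | 79% |
| 0.01 | 67% | 65% |
| 0.02 | 57% | 55% |

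**6. Difference in change between two waves.** With area ICC 0.1 and m children per area per wave, the variance per area = 2 × 0.8649 × [0.1 × (1 − r) + 0.9/m], where r is the between-wave correlation of area means. The document gives no r, so these are assumed values (12 v 11, t).

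| r | Power, m = 100 |
|---|---|
| 0.5 | 25% |
| 0.8 | 45% |
| 0.9 | 62% |
| 0.95 | 75% |

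For this contrast more children can help. At r = 0.9, power rises from 62% at m = 100 to 74% at 200, 78% at 300 and 83% at 600.

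**7. Matching.** If 12 pairs are assumed, 100 children per area give 72% at a within-pair correlation of 0.8 and 88% at 0.9 (t, 11 df). These correlations are also assumptions.

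**The case against.** The strongest reply is that the trial will not be analysed as the sample-size paragraph describes. Areas were matched on socio-demographic indices and adult risk-factor prevalence, and the growth model uses three waves. Both can remove between-area variance, and with a high enough correlation power approaches or passes 80%. The figure of 25 per grade is also a minimum, since all students in the target grades of the sampled schools are invited, and for a change contrast larger numbers can matter. This stands. A reader might infer from step 1 that the trial has only a 28% chance of detecting 0.18, or that no number of children could ever bring it to 80%. The document does not support either inference: the 30–32% ceiling belongs to the single-time comparison alone. The calculation, however, takes no credit for matching or repeated waves, and gives no figure for either.

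A second reply is that 0.1 is really a school-level ICC, since it comes from school-based research. With no area-level correlation this gives 81% for 12 v 12, close to the stated 80%, so a mix-up of levels is a plausible origin. It cannot be confirmed, and it would still be a defect: areas were randomised, and an area ICC of only 0.01 lowers power to about 65% for 12 v 11.

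A third reply is that an article may leave detail to a fuller protocol. That is fair for the between-wave correlation, whose absence is not counted as a separate fault. It does not excuse a printed set of inputs that contradicts the printed result.

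**Conclusion.** The stated 80% power and the requirement of 25 children per grade do not follow from the inputs given with them. For the comparison described, those inputs give about 28% (t) or 30% (normal) with 12 v 12 areas, and about 27% with 12 v 11. This rests on a two-sided 0.05 test, 0.1 read as an area-level ICC as the text presents it, and 100 children per area.

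The two-sided routes back to about 80% are a school-level ICC with no area correlation, or a change analysis or matching that removes most of the between-area variance. The calculation states none of these. The finding is that the justification fails. What power the planned growth model will have cannot be settled from this document, and the assumed ranges above are wide.

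**What to change.** 1. Withdraw the statement that 80% power and 25 children per grade are supported by these inputs.
2. State whether 0.1 is a school-level or an area-level ICC. If it is school-level, give a separate area-level value.
3. Restate power and the detectable difference for 12 v 11 areas and for the contrast actually tested, the difference in change over waves. Separate the school and area levels, and give a sensitivity range for the between-wave area correlation, for example 0.5 to 0.95. If credit is taken for matching, state the assumed correlation.

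The 27% figure should not simply be printed in place of 80%, because it belongs to a single-time comparison that is not the planned test.

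The cost is a recalculation and a reworded paragraph. No areas or children need to be added. The only loss is that the stated power becomes less favourable.
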